### Randomization and blinding

A table of random numbers will be generated by a third party who will not participate in the trial, using SPSS 20.0 software (SPSS Inc., Chicago, IL, USA) Additional file 2. The randomization program will be concealed in an opaque envelope and managed by the third party. At 5–10 minutes prior to the acupuncture treatment, the acupuncturist will inform the manager of the randomization program about the patient number and name via telephone; the acupuncturist will then be informed of the patient’s randomization number and treatment group. Only the acupuncturist is permitted to contact the manager Additional file 2.

A three-way separation (patients, the acupuncturist, and the recorder) will be performed for blinding. All patients as well as the recorder will be blinded to information about the randomization and the received treatment, which is only known to the acupuncturist. During the treatment, the recorder will be isolated from the operator with a screen and ear plugs. In addition, the *De Qi* group and the control group will be represented as A and B, respectively, for data analysis to ensure the objectivity of the statistician from the third party who does not participate in the procedure. Before analysis, all data will be kept by designated personnel. Unblinding will not be done until the completion of data analysis Additional file 2.

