**Fig. 2 Fig2:**
[figure not shown]
Location of acupoints. Five points are used for each patient. They are *Dubi* (ST35), *Neixiyan* (EX-LE5), *Heding* (EX-LE2), *Yinlingquan* (SP9), and *Yanglingquan* (GB 34)

In the *De Qi* group, disposable acupuncture needles (Φ0.25 × 40 mm; Suzhou Dongbang Acupuncture Inc., Suzhou, China, 215144) will be inserted vertically to a depth of 25–30 mm after sterilization of the target acupoints. Then the needles will be manipulated using techniques including lifting, thrusting, twisting, and rotating, until *De Qi* is achieved. During the treatment session, the acupuncturist will manipulate the needles every 10 minutes to maintain the intensity of the *De Qi* sensations.

In the control group, shorter disposable acupuncture needles (Φ0.25 × 25 mm; Suzhou Dongbang Acupuncture Inc., Suzhou, China, 215144) will be inserted vertically to a depth of 1–2 mm and left in position for 30 minutes without any manipulation.

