#### Assessment of De Qi sensation induced by acupuncture

In our study, the assessment of *De Qi* sensation perceived by the patients is based on the Chinese version of the ”modified” Massachusetts General Hospital Acupuncture Sensation Scale (C-MMASS) (see Additional file 1). Before the trial, the concept of “*De Qi* and its correlated sensations” will be explained to all participants by the recorder. At the end of each treatment session after the removal of the needles, patients will be asked to fill in the C-MMASS form to evaluate the intensities of 11 acupuncture sensations: soreness, aching, deep pressure, heaviness, fullness/distension, tingling, numbness, dull pain, warmth, cold, and throbbing. The intensities of these sensations are evaluated on a 0–10 cm VAS, where 0 represents “none” and 10 represents “intolerably strong sense.” There is also an additional blank row at the end of the form that the patient can use to assess any other sensations. The MASS index will then be calculated.

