### Statistics

All data will be analyzed using SPSS for Windows 17.0 Software (SPSS Inc., Chicago, IL, USA). For the main analysis, we will perform both an intent-to-treat principle and a per-protocol analysis. Measurement data will be described with mean ± standard deviation ($$ \overline{x} $$ ± SD), and count data will be expressed with number of cases and percentages. All statistical analyses will use two-tailed tests, and the level of significance will be set at *p* < 0.05 Additional file 2. 

Demographic and baseline characteristics of study participants by randomization group will be analyzed by an independent sample *t* test, *t*' test, or nonparametric test. In the comparison between the *De Qi* and control groups, the primary outcome (VAS scores) and secondary outcome (KOOS, in the form of symptom scores) will adopt the method of within-subject 6 × 2 factorial repeated measures analysis of variance (ANOVA) to analyze the integral analgesic effect, where the factors are time (six levels: baseline, and at the end of the 1^st^, 3^rd^, 6^th^, 9^th^, and 12^th^ treatments) and group (two levels: *De Qi* group and the control group). The immediate analgesic effect will be evaluated by the VAS score after the first treatment; the accumulated analgesic effect will be rated by the VAS score after the last treatment. They will be analyzed by the independent sample *t* test and *t*' test or nonparametric test. In addition, the overall *De Qi* scores of each group, i.e., the sum of the scores of all sensations in each treatment, will be considered and analyzed with the primary outcome by a bivariate correlation test (described by *r* and *p*).

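### The code meant to blind the statistician is printed with its key, and the planned De Qi analysis would very probably reveal the arms in any case, so the blind cannot last through the whole analysis as promised

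*Protocol article*

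**What the plan says.** Under Randomization and blinding, the De Qi arm is named first: this "group and the control group will be represented as A and B, respectively, for data analysis to ensure the objectivity of the statistician", who is described as coming from a third party outside the procedure. The same section adds: "Unblinding will not be done until the completion of data analysis".

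Under Assessment of De Qi sensation, after each session "patients will be asked to fill in the C-MMASS form to evaluate the intensities of 11 acupuncture sensations". Under Statistics, a bivariate correlation with VAS is planned, in which the C-MMASS "scores of each group, i.e., the sum of the scores of all sensations in each treatment, will be considered and analyzed with the primary outcome".

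Under Interventions, the De Qi arm is needled to 25–30 mm. "Then the needles will be manipulated using techniques including lifting, thrusting, twisting, and rotating, until" De Qi is obtained, with repeat manipulation every 10 minutes. Control needles "will be inserted vertically to a depth of 1–2 mm and left in position for 30 minutes without any manipulation".

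**The concern.** A coded analysis blinds the analyst only if the analyst cannot decode it. Here the key is fixed and printed. In addition, one of the planned analyses uses, by group, the variable that the two techniques are meant to separate. The article therefore claims a property, a statistician blinded until analysis is complete, that the plan as written does not deliver.

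What is at stake is limited. The Statistics section leaves some judgement to the analyst: a t, t' or nonparametric test for the immediate and accumulated VAS comparisons, and in practice who counts as per-protocol. Blinding the analyst is one guard against settling such matters with the arms in view. A report that called the analysis blinded would also be claiming more than the plan supports.

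**Working it through.** The plan gives no figure on this point, so there is none to reproduce. The check has two steps.

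**Step 1: does the label conceal the arm?** The coding sentence lists the groups in the order De Qi, control and the codes in the order A, B, and ties the two lists together in that order. Hence A = De Qi and B = control. Nothing elsewhere in the article says that the code is drawn at random, sealed, or different in practice. For a reader of that sentence, the label carries the same information as the arm name.

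**Step 2: would a neutral code last to the end of the analysis?** To relate De Qi scores to VAS, group by group, the analyst needs the scores, the VAS values and the group code. The question is how reliably the group with the higher mean De Qi score is the De Qi arm.

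Inputs:
- Patients per arm: 88 in total at 1:1 gives 44 (Sample size section). With the allowed 20% loss, 88 × 0.8 = 70.4, or about 35 per arm.
- Standardised difference *d* in mean De Qi score between arms: not given in the article, so it is an assumption and is shown over a range.

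Formula, for two arms of *n* with equal SDs and approximately normal means:

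P(De Qi arm has the higher mean) = Φ(*d* × √(*n*/2))

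For *n* = 44, √22 = 4.690. At *d* = 0.5 the argument is 0.5 × 4.690 = 2.345, and Φ(2.345) = 0.990. For *n* = 35, √17.5 = 4.183. At *d* = 0.5 the argument is 2.092, and Φ(2.092) = 0.982.

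| Assumed *d* | 44 per arm | 35 per arm |
|---|---|---|
| 0.2 | 0.826 | 0.799 |
| 0.3 | 0.920 | 0.895 |
| 0.5 | 0.990 | 0.982 |
| 0.8 | above 0.999 | above 0.999 |

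One arm is manipulated until De Qi appears, and the other is needled superficially to avoid it. A small *d* would mean that the intervention contrast had largely failed. If the contrast works as intended, the scores identify the arms almost surely. The De Qi correlation is part of the data analysis, and unblinding is barred until that analysis is complete. Without staged release of the data, both cannot hold, and the article describes no staging.

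**The case against.** The strongest case on the other side has five parts.

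- **The ordered listing of A and B may be loose wording** for plain group labels, and the statistician, who is outside the procedure, may never see the article. That is possible. The sentence still states a key, and nothing else in the article withdraws it.
- **Early disclosure is not shown.** A reader might infer that the De Qi scores sit in the same file as VAS and reveal the arms before the VAS comparison is done. The article describes neither data files nor an order of work, and it lists the De Qi correlation last. This objection stands. The text supports only that the blind cannot survive the whole analysis.
- **The room for choice is easily overstated.** A reader might multiply three test forms by two populations and count six open versions of each comparison. That is wrong, because intention-to-treat and per-protocol analyses are both committed. The repeated-measures ANOVA of VAS and KOOS also has a single named form. What remains is the t, t' or nonparametric choice and per-protocol membership, and a full protocol or analysis plan may settle both.
- **Picking the smallest p-value needs no knowledge of which arm is which.** This is true, and a pre-stated rule for choosing the test is the direct remedy. Knowledge of the arms matters for choices that favour a direction.
- **Some unmasking is inherent in a trial about De Qi.** This is also true, and it is a reason to say when the blind ends instead of promising that it lasts to the end.

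**Conclusion.** The point holds in a narrow form and is minor. As written, the statistician's code conceals nothing from anyone who has read the article. Even a neutral code would very probably be broken once De Qi scores are analysed by group: the probability is about 0.98 to 0.99 at an assumed difference of 0.5 SD, and 0.80 to 0.83 at only 0.2 SD. The first conclusion rests on the wording alone. The second rests on an assumed separation that the article does not quantify, although the techniques are designed to produce one.

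A reader might go further and conclude that the analysis was biased or that the trial's blinding as a whole fails. The article supports neither. No bias is shown, the VAS is reported by the patient, and the stated blinding of patients and recorder is unaffected. No estimate or sample size changes.

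**What to change.** Four changes, all to wording and data handling:

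1. Delete the fixed mapping. Have someone other than the analyst assign the two codes at random and hold the key. Name that role explicitly: the statistician is said to come from the third party, the same term used for whoever generates the random numbers and manages the allocation, and the text does not separate these tasks.
2. Fix the rule for choosing among the t, t' and nonparametric tests, and fix the per-protocol set, before C-MMASS data are released.
3. Run and lock the VAS and KOOS between-group analyses on an export without C-MMASS, then release C-MMASS for the De Qi analyses.
4. State that the statistician's blind ends at that release. If staging is not wanted, describe the statistician as not blinded.

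The cost is a short protocol revision and two data exports instead of one. Patients and the site are not affected. At the stage given under Trial status, with treatment and follow-up still under way, the change could still be made before analysis.

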### Researchers

Treatments will be performed by a licensed acupuncturist with more than 6 years’ experience. Two supervisors will monitor the procedure throughout the study. The acupuncturist and other researchers responsible for data collection will be trained before the trial.

### Interventions

The acupoints *Dubi* (ST35), *Neixiyan* (EX-LE5), *Heding* (EX-LE2), *Yinlingquan* (SP9), and *Yanglingquan* (GB 34) will be used for each patient. According to the National Standard of The People’s Republic of China. The Name and Location of Acupoints, issued in 2006 (GB/T 12346-2006), *Dubi* (ST35), also called *Waixiyan*, is located in a depression lateral to the patellar ligament. *Neixiyan* (EX-LE5) is located in the center of the depression of the patellar ligament of the knee and is opposite ST35. *Heding* (EX-LE2) is located in the depression above the midpoint of the superior patellar border. *Yinlingquan* (SP9) is located in the depression between the lower border of the medial condyle of the tibia and the medial border of the tibia. *Yanglingquan* (GB 34) is located in the depression anterior and inferior to the head of the fibula (Fig. 2) Additional file 2.

**Fig. 2 Fig2:**
[figure not shown]
Location of acupoints. Five points are used for each patient. They are *Dubi* (ST35), *Neixiyan* (EX-LE5), *Heding* (EX-LE2), *Yinlingquan* (SP9), and *Yanglingquan* (GB 34)

In the *De Qi* group, disposable acupuncture needles (Φ0.25 × 40 mm; Suzhou Dongbang Acupuncture Inc., Suzhou, China, 215144) will be inserted vertically to a depth of 25–30 mm after sterilization of the target acupoints. Then the needles will be manipulated using techniques including lifting, thrusting, twisting, and rotating, until *De Qi* is achieved. During the treatment session, the acupuncturist will manipulate the needles every 10 minutes to maintain the intensity of the *De Qi* sensations.

In the control group, shorter disposable acupuncture needles (Φ0.25 × 25 mm; Suzhou Dongbang Acupuncture Inc., Suzhou, China, 215144) will be inserted vertically to a depth of 1–2 mm and left in position for 30 minutes without any manipulation.

### Outcomes

#### Initial visit

The researchers will collect the clinical information of the patients during their initial visits, including age, sex, course of disease, and body mass index. The participants will not yet be assigned to a treatment group at this time Additional file 2.

#### Knee pain intensity

To evaluate the efficacy of acupuncture treatment for KOA, knee pain intensity is measured via a 0–100 mm visual analog scale (VAS). The patient moves the slider on a 100-mm VAS ruler to indicate the intensity of knee pain that he/she is suffering, where the left end of the ruler marks “no pain,” and the right end marks “intolerable pain.” The distance (in millimeters) from the slider to the left end of the ruler is read directly from the back of the ruler by the researcher and is used as the VAS score for pain intensity, which is the primary outcome index in this study. The VAS score for knee pain intensity will be measured before each treatment and at the end of the 1^st^, 3^rd^, 6^th^, 9^th^, and 12^th^ treatments, as well as at the end of the follow-up visit (Fig. 3). Additional file 2

**Fig. 3 Fig3:**
[figure not shown]
Planned visit schedule of enrollment, interventions, and assessments. Notes: ****t***
_***13***_ is at the end of the follow-up (i.e., the 8th week). *VAS* visual analog scale, *KOOS* Knee injury and Osteoarthritis Outcome Score, *C-MMASS* Modified-Chinese version of the Massachusetts General Hospital Acupuncture Sensation Scale

#### Knee injury and Osteoarthritis Outcome Score (KOOS)

The KOOS [23] is used as the secondary clinical outcome. The KOOS comprises of five subscales, each of which produces an outcome score. These subscales include pain, other relevant symptoms, activities of daily living (ADL), function in sports and recreation, and knee-related quality of life (QOL). Trained research assistants, who are blinded to the treatment, will measure the KOOS for all patients both at the baseline and at the end of the 1^st^, 3^rd^, 6^th^, 9^th^, and 12^th^ treatments and at the end of the follow-up (Fig. 3) Additional file 2. For each subscale, the outcome score will be normalized, where 0 indicates no symptoms and 10 indicates the most extreme symptoms [23].

#### Assessment of De Qi sensation induced by acupuncture

In our study, the assessment of *De Qi* sensation perceived by the patients is based on the Chinese version of the ”modified” Massachusetts General Hospital Acupuncture Sensation Scale (C-MMASS) (see Additional file 1). Before the trial, the concept of “*De Qi* and its correlated sensations” will be explained to all participants by the recorder. At the end of each treatment session after the removal of the needles, patients will be asked to fill in the C-MMASS form to evaluate the intensities of 11 acupuncture sensations: soreness, aching, deep pressure, heaviness, fullness/distension, tingling, numbness, dull pain, warmth, cold, and throbbing. The intensities of these sensations are evaluated on a 0–10 cm VAS, where 0 represents “none” and 10 represents “intolerably strong sense.” There is also an additional blank row at the end of the form that the patient can use to assess any other sensations. The MASS index will then be calculated.

#### Side effects

Any adverse events such as fainting, hematoma, and local infection during acupuncture will be recorded and analyzed Additional file 2.

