**Methods/design:**

Eighty-eight patients with KOA will be recruited and randomly assigned to the *De Qi* group (enhanced stimulation to evoke *De Qi*) and the control group (weak stimulation to avoid *De Qi*) in the Department of Acupuncture and Physical Therapy, Beijing Luhe Hospital Affiliated to Capital Medical University. Each patient will receive three 30-minute sessions per week for 4 consecutive weeks and undergo a 1 month follow-up. The severity of knee pain, as measured on a 100-mm visual analog scale (where 0 indicates no pain and 100 indicates intolerable pain) will be used as the primary outcome, and the Knee injury and Osteoarthritis Outcome Score will be used as the secondary outcome. Both indexes will be measured before and after the 1^st^ (for evaluating the immediate analgesic effects), 3^rd^, 6^th^, 9^th^, and 12^th^ (for evaluating the accumulated analgesic effects) treatments and at the end of the follow-up. The intensity of the *De Qi* sensation will be assessed by the Chinese-Modified Massachusetts General Hospital Acupuncture Sensation Scale at the end of each treatment. Side effects during the treatments will be recorded and analyzed as well. The comparisons between the *De Qi* group and the control group will be done by using both an intention-to-treat analysis and a per-protocol analysis.

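### The stated adverse-event window stops at treatment, so the one-month follow-up, including delayed effects of the last sessions, falls outside it

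*Protocol article*

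**What the plan says.** The article describes safety recording twice. Under Outcomes, Side effects: "Any adverse events such as fainting, hematoma, and local infection during acupuncture will be recorded and analyzed". In the Methods/design paragraph of the Abstract: "Side effects during the treatments will be recorded and analyzed as well".

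The same Abstract paragraph sets out the time on study: "Each patient will receive three 30-minute sessions per week for 4 consecutive weeks and undergo a 1 month follow-up". The note to Fig. 3 places the end of follow-up at week 8.

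The efficacy measures are timed differently. Under Knee pain intensity, "The VAS score for knee pain intensity will be measured before each treatment", then after selected sessions, "as well as at the end of the follow-up visit". The KOOS section likewise includes the end of follow-up.

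The Interventions section separates the arms by depth and manipulation. De Qi needles "will be inserted vertically to a depth of 25–30 mm after sterilization of the target acupoints" and are then manipulated, again every 10 minutes. Control needles "will be inserted vertically to a depth of 1–2 mm and left in position for 30 minutes without any manipulation".

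**The concern.** The article does more than stay silent on the timing of adverse-event recording. It states a limit, twice, and that limit ends with treatment although patients remain on study for another month and are seen at the end of it. An event that follows one of the last sessions and appears after the course has ended need not be recorded by anyone who follows these words.

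The wording also sits awkwardly with its own examples. Local infection is named as an event to capture, yet it would hardly show while the needles are in place. Staff could reasonably differ on whether an event reported at the next visit counts.

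At stake is the completeness of the safety comparison. One arm receives deep, repeatedly manipulated needling and the other shallow needling left alone. If delayed tissue events are under-recorded, the loss need not be equal between arms.

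**Working it through.** The plan gives no figure on this point (no event rate, no expected count, no safety threshold), so there is none to reproduce. The check compares the wording and then works out what each reading covers.

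**Inputs.** Three sessions a week for 4 weeks, 30 minutes each, then a month of follow-up (Abstract); end of follow-up at week 8 (note to Fig. 3). The Overview gives 14 weeks in total, which its own parts (2 weeks, 4 weeks and 1 month) do not reach. I use week 8; the conclusion does not depend on it.

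**Step 1: what the wording can mean.**
- *Session reading.* In the Abstract, treatments are numbered sessions: measurements are taken around the 1st to the 12th, and De Qi is scored at the end of each one. Randomization and blinding also uses the word for a single session, when the recorder is screened off.
- *Course reading.* The Background uses acupuncture treatment of KOA for the therapy as a whole, and naming local infection makes sense only if more than needle-in time is meant.

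The infection example favours the course reading. The wording does not decide it.

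**Step 2: what each reading covers.**

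| Reading | Inside the window | Between sessions | Follow-up month |
|---|---|---|---|
| Session | 12 × 0.5 h = 6 h | outside | outside |
| Course | 4 weeks | inside | outside |

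The last column is the same on both readings. The point rests on that.

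**Step 3: shares of time.**
- Session reading: 6 h / (8 × 7 × 24 h) = 6 / 1344 = 0.45% of the eight weeks, or 6 / (4 × 7 × 24 h) = 6 / 672 = 0.9% of the course.
- Course reading: (8 − 4) / 8 = about half of the eight weeks uncovered.

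These are shares of clock time. No needling is scheduled in the follow-up month, so events from needling would not be spread evenly over it.

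**Step 4: where the gap falls on the course reading.** An event after any of sessions 1 to 11 can still be noted at a later session. After session 12 there is no later treatment contact, so at least 1 of 12 sessions has no later contact within the window. Slower events after the other sessions of week 4 may also appear too late.

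**Step 5: existing contacts.** Patients are seen before each of the 12 sessions and at the end of follow-up, because VAS is measured then. The article does not say that they are asked about events at any of these contacts.

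**The case against.** The strongest reply is that both sentences are one-line summaries in a condensed article. Neither says that recording is confined to the stated period. The Side effects sentence points to an additional file, and Fig. 3, which holds the assessment schedule, is not shown here. Procedures for asking about events are the kind of detail that an article leaves to the full protocol. Moreover, the stated aim is analgesic effect, and no safety hypothesis or threshold depends on this wording.

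Part of this stands. One cannot conclude that adverse events were in fact not collected at follow-up, and the absence of a described questioning procedure is not itself a fault. What does not fall away is that the article names a period, and does so in the same Abstract paragraph that takes VAS and KOOS to the end of follow-up.

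A reader might infer two stronger things. The first is that infections and haematomas between sessions are missed. That requires the session reading, which the infection example speaks against; they may be missed, no more. The second is that missed events probably cluster in the De Qi arm. Depth and manipulation make that plausible, but the article gives no rate or timing for either arm, and the recording sentence treats the arms alike.

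**Conclusion.** The point holds in a limited form. As worded, the adverse-event window leaves out the one-month follow-up on either reading, and with it delayed effects of the last sessions. Loss of between-session events is possible on the narrower reading and is not established. Unequal under-recording between arms is an inference of unknown size.

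The 0.45% and one-half figures describe time outside the window. A reader might take them as the proportion of events lost or as the size of a bias; the documents support neither. The conclusion assumes that the article's wording reflects the full protocol, which is not at hand. It is a cheap improvement to safety capture and does not affect the analgesic comparison.

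**What to change.** State that adverse events are recorded from the first needling to the week-8 follow-up visit. Ask one standard question, in the same words in both arms, before each session (covering the interval since the last one) and at the follow-up visit already planned. Report the events by arm.

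Trial status says that recruitment is complete and that treatment and follow-up are still in progress, so the question can be added only to the visits that remain. For visits already past, the report should state the window actually used.

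The cost is one question at contacts that already take place and a little extra data entry. No visit is added, and the efficacy analysis does not change.
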